#### *Cost-effectiveness*

We will perform a cost-utility analysis alongside the trial from a societal perspective with a time horizon of one year comparing active cTBS to sham cTBS. In a scenario analysis, we will show the impact on cost-effectiveness, if effects at one year would be extrapolated over time. Sham stimulation could have a placebo effect; however, the magnitude of the placebo effect is unsure. A scenario analysis will be performed to show the potential impact of the placebo effect on cost-effectiveness results.

Quality of life will be assessed by combining mortality and quality of life using an area-under-the-curve approach. Quality of life will be assessed with the EQ-5D-5L. The Dutch tariffs will be used to calculate answer into a utility score. This utility score can range up to 1, in which 0 corresponds to death and 1 corresponds to perfect health.

Costs of the interventional procedures itself will be calculated with a bottom-up approach or estimated based on financial information from the rehabilitation centers. In a scenario analysis, we will estimate cost-effectiveness if we exclude navigation costs during the procedure.

Other healthcare resource use will be assessed in two ways. Direct healthcare costs during clinical rehabilitation will be estimated for each center based on the length of stay (LOS) of a patient. LOS will be calculated based on the date of admission and the date of discharge at the rehabilitation center. These dates will be requested from the administrative department of each rehabilitation center. Healthcare costs after clinical rehabilitation will be collected through CASTOR at 6 and 12 months post-stroke using an adaptation of the iMTA Medical Consumption Questionnaire (iMCQ). Data will be extrapolated to fill in missing data caused by the recall-period of three months. The iMCQ will be used to measure all direct medical costs (consultations, hospitalizations), and direct non-medical costs (family care). Healthcare resource use will be multiplied with Dutch unit costs to determine healthcare costs. Unit costs will be used as described in the Dutch Costing guideline; NZA tariffs or internal UMCU tariffs if both are missing.

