## 8.2 Randomization, blinding and treatment allocation

Patients will be randomly allocated to receive active or sham continuous theta burst stimulation (cTBS) treatment. Randomization will be executed through a web-based allocation service (CASTOR) that generates a unique study number for each participant. Randomization is stratified based on the ability to extend one or more fingers of the paretic arm and the rehabilitation center at which the participant is recruited. Information on treatment allocation will be kept separate from the main study database. Patients will be randomly allocated to group A or group B, to allow double-blinding.

Sham cTBS will be performed using a sham TMS coil, which looks identical to an active TMS coil but does not produce effective stimulation. The sham and active TMS coils will be labeled with a code (A/B) by the coordinating investigator who is not involved in any of the TMS treatments. The TMS therapist performs randomization and patients will be allocated to receive treatment with coil A or B, depending on their group allocation (A/B). Therefore, the TMS therapists and patients are unaware of treatment allocation. Blinding of the patient and therapist will be maintained until the last patient has completed the final follow-up (at 12 months post-stroke). Only one of the coordinating investigators can link treatment allocation to the active or sham condition. The independent trial statistician will combine data on treatment allocation with the clinical data to report to the data safety monitoring board (DSMB). The treatment allocation code will not be broken until the database has been locked, which is after the all data have been cleaned. The moment of datalock is defined in the statistical analysis plan. Cleaning of the data will be performed by a coordinating investigator who is unaware of treatment allocation.

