### **10.3 Secondary study parameter(s)**

Secondary endpoints are the FM-UE at 12 months post-stroke and the ARAT, NHPT, mRS, SIS-hand, SIS-participation and the EQ-5D at 90 days and 12 months post-stroke. These secondary endpoints are analyzed using a mixed model repeated measures or cumulative link mixed model, depending on the nature of the outcome measure. The model includes the baseline score; the stratification factor (ability versus no ability to

extend 1 or more fingers), visit (90 days and 12 months post-stroke), and the interaction of treatment (sham cTBS; active cTBS) by visit. The model includes a random effect for rehabilitation center. Additional model parameters and predefined subgroup analyses are described in the SAP.

The length of stay will be analyzed using a two-sample independent t-test.

Ipsilesional excitability will be analyzed using a linear mixed model. The outcome variable is the ipsilesional RMT after the final cTBS session. The model includes fixed effects for the ipsilesional RMT before the first cTBS session, stratification factor (ability versus no ability to extend 1 or more fingers) and treatment (sham cTBS; active cTBS) and a random effect for rehabilitation center.

Contralesional excitability before the 1st, 6th and 10th cTBS session will be analyzed using a mixed model for repeated measures. The outcome variable is the contralesional RMT determined before the 1st, 6th and 10th cTBS session. The model includes fixed effects for baseline RMT, cTBS session number (1, 6 or 10) and type of treatment (sham cTBS; active cTBS) and a random effect for rehabilitation center.

Contralesional inhibition after the 1st, 6th and 10th cTBS session will be analyzed using a mixed model for repeated measures. The outcome variable is the contralesional MEP amplitude after cTBS. The model includes fixed effects for and the contralesional MEP amplitude, cTBS session (1, 6 or 10) and treatment (sham cTBS; active cTBS) and a random effect for rehabilitation center.

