### **11.2 Recruitment and consent**

Patients potentially eligible for participation will be approached by the treating rehabilitation physician. The treating rehabilitation will ask the patient whether the local investigator can approach him or her. Patients will be screened for eligibility by the local investigator based on the inclusion and exclusion criteria, which includes eligibility according to the TMS safety questionnaire. If the patient is eligible, the local investigator explains the study procedures and provides the eligible patient with the patient information letter. The local investigator encourages the patient to read the information, discuss the content with friends or relatives and to write down questions that may arise. The patient will be given time to consider participation. During a second consultation with the local investigator, the investigator will give the patient the opportunity to ask questions, after which the patient can provide written informed consent. In case the patient does not have the capacity to provide written informed consent (e.g., due to upper limb impairments or aphasia), his/her representative may provide written informed consent. As soon as the patient has regained capacity, he/she will be asked for written informed consent. The patient will be provided with a copy of the signed informed consent.

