## 2. Study design

B-STARS2 is a multi-centre, double-blind, randomised, sham-controlled, clinical trial.

Participants will be recruited from 16 rehabilitation centres in the Netherlands over a period of 51 months (Q2 of 2024 to Q4 of 2028). The total duration of follow-up for each participant is until one year after stroke. The total study duration is 63 months.

Baseline assessment will be performed before the start of the intervention, which must occur within 21 days after stroke onset. Follow-up assessments will be performed at 90 days (+/- 7 days) and 12 months (+/- 14 days) post-stroke (Figure 1).

The intervention consists of ten daily sessions of active or sham cTBS, delivered over the contralesional primary motor cortex, started within 21 days post-stroke and combined with regular care upper limb therapy.

Participants are randomly assigned in a 1:1 ratio to one of the two treatment groups (group A or B) using a web-based data management service. Treatment allocation is stratified by rehabilitation centre and the ability to extend one or more fingers of the affected hand.

An independent DSMB is monitoring the safety of participants of the trial. The DSMB meets at least annually. An independent statistician will perform unblinded interim analyses on all reported (serious) adverse events after 150 and 300 patients have completed the 90 days post-stroke follow-up. The independent statistician will report the outcome of the interim analyses directly to the DSMB, as well as listings of all SAE reports and unblinded aggregate summaries of data by treatment group for review in closed meetings. Feedback, blind to treatment, will be provided in written conclusions to the B-STARS2 project leaders.

[figure not shown]

**Figure 1.** Study timeline.

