### 7.5. Secondary analyses

The FM-UE, ARAT, NHPT, mRS, SIS-hand and SIS-participation and EQ-5D-5L at 90 days and 12 months post-stroke will be assessed using a mixed model for repeated measures or cumulative link mixed model, depending on the type of outcome measure. The outcome variable is the secondary outcome. The model includes fixed effects for the corresponding baseline scores; the stratification factor (ability versus no ability to extend one or more fingers), age, gender, stroke subtype (ischemic stroke vs. Intracerebral haemorrhage), visit (90 days; 12 months) and the interaction of treatment (sham cTBS; active cTBS) by visit and random effects for rehabilitation centre.

The length of stay will be analysed using a two-sample independent t-test.

Ipsilesional excitability will be analysed using a linear mixed model. The outcome variable is the ipsilesional RMT after the final cTBS session. The model includes fixed effects for the ipsilesional RMT before the first cTBS session, stratification factor (ability versus no ability to extend 1 or more fingers) and treatment (sham cTBS; active cTBS) and random effects for rehabilitation centre.

Contralesional excitability before the 1st, 6th and 10th cTBS session will be analysed using a mixed model for repeated measures. The outcome variable is the contralesional RMT determined before the 1st, 6th and 10th cTBS session. The model includes fixed effects for baseline RMT, cTBS session

number (1, 6 or 10) and type of treatment (sham cTBS; active cTBS) and random effects for rehabilitation centre.

Contralesional excitability after the 1st, 6th and 10th cTBS session will be analysed using a mixed model for repeated measures. The outcome variable is the contralesional MEP amplitude after cTBS. The model includes fixed effects for the contralesional MEP amplitude before cTBS, cTBS session (1, 6 or 10) and treatment (sham cTBS; active cTBS) and random effects for rehabilitation centre.

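### Length of stay is compared with an unadjusted t-test although randomisation is stratified: the test is valid, but conservative and less precise than the data allow

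*Combined protocol and SAP*

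**What the plan says.** - **Analysis.** SAP 7.5: "The length of stay will be analysed using a two-sample independent t-test". Protocol 10.3: "The length of stay will be analyzed using a two-sample independent t-test". Neither adds a covariate, a centre term or a sensitivity analysis for this outcome.
- **Randomisation.** Protocol 8.2: "Randomization is stratified based on the ability to extend one or more fingers of the paretic arm and the rehabilitation center". SAP 2 agrees: "Treatment allocation is stratified by rehabilitation centre and the ability to extend one or more fingers of the affected hand". SAP 2 also gives the ratio and the number of sites: "Participants are randomly assigned in a 1:1 ratio to one of the two treatment groups"; "Participants will be recruited from 16 rehabilitation centres in the Netherlands".
- **Other outcomes in SAP 7.5.** The clinical scores and questionnaires are modelled with their baseline value, finger extension, age, gender, stroke subtype and a random centre effect. The excitability outcomes have at least a baseline value and a random centre effect. Length of stay is the only outcome analysed there with no centre term and no covariate.
- **Sensitivity.** The optional adjustment for imbalanced baseline characteristics in SAP 7.6 refers to the SAP 7.4 model for the FM-UE, not to length of stay.
- **Definition.** Protocol 8.1.2, under cost-effectiveness: "LOS will be calculated based on the date of admission and the date of discharge at the rehabilitation center".
- **Status.** SAP 4 lists length of stay among the additional secondary outcomes.

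**The concern.** Stratified allocation balances the arms within each centre and finger-extension stratum. Differences between strata then add little to the real sampling error of the treatment difference. The two-sample t-test still counts all of that variance in its standard error, so it reports more uncertainty than there is. Baseline severity, age and stroke subtype are not balanced by design. Leaving them out gives up precision that adjustment would recover.

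Both losses are likely here, because discharge plausibly depends on centre practice and on initial impairment. That is a judgement; the documents do not quantify it. At stake are the power and interval width for an outcome on which the protocol repeatedly cites an 18-day reduction from a single-centre phase II trial of 60 patients.

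**Working it through.** **1. The plan's own figure.** There is none for length of stay: no standard deviation, power or sample size. The primary sample size (Protocol 4.4) does reproduce. With a difference of 6.6, SD 23, two-sided alpha 0.05 and power 0.85, the t-based calculation gives 438.07 in total, or 219.03 per arm. Rounded up to 220 per arm, that is the stated 440, used below.

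**2. Formulas.** Let R² be the share of length-of-stay variance explained by centre, finger extension and baseline covariates.
- Adjusted SE / t-test SE = √(1 − R²)
- Equivalent sample size under the t-test = 440 / (1 − R²)
- 95% half-width = 1.96 × SD × √(4/440) × √(1 − R²)

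R² and the SD are assumptions, shown as ranges. The 9-day difference, half the phase II effect, is also an assumption.

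| R² | SE ratio | SE reduction | Equivalent N | Half-width, SD 35 (days) | Power for 9 days, SD 35 | Power for 9 days, SD 45 |
|---|---|---|---|---|---|---|
| 0 (t-test) | 1.000 | – | 440 | 6.5 | 76.9% | 55.5% |
| 0.05 | 0.975 | 2.5% | 463 (+5%) | 6.4 | 79.0% | 57.6% |
| 0.10 | 0.949 | 5.1% | 489 (+11%) | 6.2 | 81.1% | 59.9% |
| 0.20 | 0.894 | 10.6% | 550 (+25%) | 5.9 | 85.4% | 65.0% |
| 0.30 | 0.837 | 16.3% | 629 (+43%) | 5.5 | 89.7% | 70.8% |
| 0.40 | 0.775 | 22.5% | 733 (+67%) | 5.1 | 93.6% | 77.3% |

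**3. The 18-day effect.** With 440 patients, the plain t-test has at least 96% power for 18 days at any SD up to 50, and 88% at SD 60.

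**4. Check by simulation.** The set-up was 16 centres × 2 finger-extension strata, 448 patients, SD 35 and 2,000 runs. Blocks of 4 within strata were assumed, because the documents give no block size. The adjusted model used fixed centre effects.

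| Variance explained: centre / finger extension / baseline | Type I error, t-test vs adjusted | Power for 9 days, t-test vs adjusted |
|---|---|---|
| 5% / 5% / 10% (total 20%) | 3.3% vs 4.1% | 77% vs 84% |
| 10% / 10% / 10% (total 30%) | 2.6% vs 4.8% | 79% vs 90% |

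In the second scenario with no treatment effect, the t-test reported an average SE of 3.30 days, while its estimate actually varied with an SD of 2.96. For the adjusted model the two figures were 2.77 and 2.75. The t-test therefore overstates its own error, and the adjusted estimate is also somewhat more precise.

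**5. Days before treatment.** The first session falls within 21 days of stroke, so the earlier part of the stay is at most 21 days. If it were uniform over 0 to 21 days, its SD would be 21/√12 = 6.06 and its variance 36.75. If it were also independent of the later stay, it would add 36.75/45² = 1.8% to 36.75/25² = 5.9% to the variance, for a later-stay SD of 45 down to 25. With a negative correlation it could lower the total.

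**The case against.** The strongest case for the plan is that the t-test is simple, unbiased and errs on the safe side. Length of stay is an additional secondary outcome with no power claim attached. If the 18-day effect is real, the test is adequate. The size of the loss rests wholly on an assumed R², and at 5% to 10% the gain is small. All of this stands, and it limits the point to efficiency. It gives no reason to leave out terms that the neighbouring analyses include.

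A reader might also infer stronger things that the documents do not support:

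- **The result would be biased or falsely positive.** The opposite holds: the type I error falls below 5%.
- **The cost-utility result is weakened.** The t-test does not feed it. The health-economic plan multiplies each patient's stay by the centre's daily cost (section 7.2) and handles uncertainty by multiple imputation and bootstrapping (section 4.1).
- **Counting from admission is a serious flaw.** Recruitment takes place through the rehabilitation team (Protocol 11.2: "Patients potentially eligible for participation will be approached by the treating rehabilitation physician"), so some days precede treatment. Their effect on variance is probably small (step 5). The full stay is also the quantity that is costed, and it matches the phase II measure.
- **A death in the centre counts as a short, favourable stay.** No section says so. SAP 6 applies a similar framework to secondary endpoints, and its only death rule concerns the FM-UE score. Silence does not establish the claim.

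**Conclusion.** The point holds as a matter of efficiency. The planned comparison of length of stay is valid and unbiased, but conservative, with a wider interval than necessary. Under the assumed R² of 5% to 40%, adjustment shrinks the reported standard error by about 3% to 23%, equal to about 5% to 67% more patients. The direction follows from the stratified design and from standard covariate adjustment. The size cannot be derived from the documents. In practice the choice matters if the true reduction is well below 18 days, which is plausible when a small single-centre result is retested in many centres, and for interval width at any effect. It changes neither the primary analysis nor the cost-utility analysis.

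**What to change.** In SAP 7.5, and to match in Protocol 10.3:

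1. Make the main analysis of length of stay a linear mixed model of the SAP 7.4 type: fixed effects for treatment, finger extension, baseline FM-UE, age, gender and stroke subtype, and a random effect for centre.
2. Report the adjusted difference in days with a robust or bootstrap 95% interval, because stays are likely to be skewed.
3. Keep the two-sample t-test as a supplementary result.
4. Keep the admission-to-discharge definition, so that the outcome and the cost input remain the same quantity. Days from admission to first session may be added as a covariate. They can be derived from the stroke-to-admission and stroke-to-cTBS times already listed in SAP 7.2.

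The cost is SAP and protocol wording plus a few lines of code; all the variables are already collected. SAP 5.1 keeps the allocation code sealed until database lock, so the change can be made blind. Made after unblinding, it would look post hoc.

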## 5. TREATMENT OF SUBJECTS

### 5.1 Investigational treatment

#### Active cTBS

The intervention consists of 10 daily sessions of active or sham cTBS, delivered over the contralesional primary motor cortex (M1) in a period of 10 consecutive working days within a period of 17 days. The first cTBS session takes place within 21 days after stroke onset. cTBS treatment will be delivered prior to at least 40 minutes of regular care upper limb therapy, with a maximum time interval between cTBS and upper limb therapy of 15 minutes. Regular care upper limb therapy will be performed according to local protocols, which are based on national guidelines from the royal Dutch Society for Physical Therapy, and will be adjusted based on the patient's level of upper limb impairment. TMS procedures will be performed in accordance with recent safety guidelines for TMS.

Stimulation location is defined as the position on the scalp at which motor evoked potentials (MEPs) with the largest peak-to-peak amplitude could be evoked in the first dorsal interosseous (FDI) muscle of the unaffected arm by delivering TMS pulses and monitoring the electromyogram (EMG). Stimulation intensity is set at 70% of the resting motor threshold (RMT), which is defined as the minimum machine output at which stimulation evokes at least 5 of 10 MEPs with a peak-to-peak amplitude of over 50  $\mu$ V with the TMS coil oriented 45 degrees to the midline and an interstimulus interval of 7s. The stimulation location and intensity are determined before the 1st, 6th and 10th cTBS session.

cTBS consists of continuous delivery of bursts of 3 biphasic stimuli at 50 Hz repeated at 5 bursts per second for a duration of 40 seconds resulting in a total of 600 stimuli. During treatment, the TMS coil is placed on the scalp and oriented at 45 degrees to the midline.

Active cTBS will be delivered using an active figure-of-eight TMS coil.

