## **13. STRUCTURED RISK ANALYSIS**

### **13.1 Potential issues of concern**

a. Level of knowledge about mechanism of action

A single TMS pulse can activate cortical neurons through electromagnetic induction. Repetitive delivery of TMS pulses can increase or reduce activity and excitability in the stimulated area depending on the stimulation paradigm, through long-term potentiation or depression (LTP/LTD) mechanisms, respectively. Stimulation paradigms such as low-frequency stimulation and continuous theta burst stimulation have been shown to reduce activity and excitability in the stimulated area. The effects of stimulation are not restricted to the stimulated area, but spread to connected brain regions.

The exact mechanism of rTMS treatment in promoting upper limb recovery is unclear. Previous neuroimaging and neurophysiological studies indicate that a motor stroke affects the balance in bilateral M1 activity, with the magnitude of the imbalance correlating with the level of impairment. Based on this evidence, it has been hypothesized that reducing contralesional M1 activity with inhibitory rTMS can promote recovery of the affected upper limb. Our phase II trial data show that inhibitory rTMS of the contralesional M1 promotes recovery of the upper limb. We also showed that treatment was associated with an increase in ipsilesional M1 excitability directly after 10 treatment sessions, providing a potential treatment mechanism.

b. Previous exposure of human beings with the test product(s) and/or products with a similar biological mechanism

TMS was invented in 1985 by Anthony Barker, after which it has been used to safely stimulate and study human motor cortex for over 35 years. TMS has been used repetitively for therapeutic purposes since its approval for the treatment of depression in 2008. Since then, several other clinical applications have been introduced, resulting in an abundance of TMS safety data.

c. Can the primary or secondary mechanism be induced in animals and/or in ex-vivo human cell material?

Yes, promotion of upper limb recovery with contralesional inhibitory rTMS can be studied in animals but not in ex-vivo human cell material.

d. Selectivity of the mechanism to target tissue in animals and/or human beings

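### The two contralesional mixed models (RMT and MEP amplitude) leave out the finger-extension stratum that randomisation uses and the plan's other mixed models keep; adding it is free, and the gain is unknown and probably small.

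*Combined protocol and SAP*

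**What the plan says.** SAP 2 gives the randomisation factors: "Treatment allocation is stratified by rehabilitation centre and the ability to extend one or more fingers of the affected hand". Protocol 8.2 agrees. Allocation is 1:1.

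The mixed models treat the finger-extension factor as follows:

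| Model | Where | Finger extension | Centre |
|---|---|---|---|
| FM-UE at 90 days (primary) | SAP 7.4, protocol 10.2 | fixed effect | random effect |
| Clinical scales at 90 days and 12 months | SAP 7.5, protocol 10.3 | fixed effect | random effect |
| Ipsilesional RMT | SAP 7.5, protocol 10.3 | fixed effect | random effect |
| Contralesional RMT | SAP 7.5, protocol 10.3 | absent | random effect |
| Contralesional MEP amplitude | SAP 7.5, protocol 10.3 | absent | random effect |

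For contralesional RMT the protocol lists: "The model includes fixed effects for baseline RMT, cTBS session number (1, 6 or 10) and type of treatment (sham cTBS; active cTBS"). For MEP amplitude the SAP lists: "The model includes fixed effects for the contralesional MEP amplitude before cTBS, cTBS session (1, 6 or 10) and treatment (sham cTBS; active cTBS"). The protocol's sentence for the MEP model is incomplete where the pre-stimulation amplitude should be named, but it does not mention the stratum either. Neither document gives a reason for the omission. Length of stay is compared by a t-test, so it is not part of this comparison of mixed models.

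**The concern.** When allocation is balanced within a factor that predicts the outcome, the treatment estimate benefits from that balance. A model that omits the factor leaves its variation in the residual. The reported standard error is then larger than the true sampling variation, and the test rejects less often than its nominal level. The usual remedy is to analyse by the factors used to randomise. The plan does this elsewhere. Even the sparse ipsilesional RMT model, which has no terms for age, gender or stroke subtype, keeps finger extension.

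The models serve a stated secondary objective, namely whether active stimulation reduces contralesional excitability during the two-week course. That is also the mechanism proposed in protocol 13.1. A link with the stratum is plausible, since that section describes an imbalance in motor cortex activity, "with the magnitude of the imbalance correlating with the level of impairment". What is at stake is a little precision on a mechanistic secondary outcome, and consistency between the analysis and the design.

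**Working it through.** **What the plan lets us check.** The only fully specified sample size nearby is the primary one. With a difference of 6.6, SD 23, two-sided 5% and 85% power, the normal formula gives 2 × ((1.960 + 1.036) × 23 / 6.6)² = 218.1, so 219 per arm (438 in total). The t-test version gives 220 per arm, which matches the stated 440. That figure does not concern the contralesional outcomes, for which the documents give no effect size, SD or power. What follows is therefore conditional.

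**Inputs.** Two-sided 5% test (z = 1.960) and a reference power of 80% with the stratum in the model (z = 0.842). R² is the stratum's share of the residual variance left after the baseline covariate and centre. It is an assumption and is shown as a range.

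**Standard error and test size.** Omitting the stratum inflates the reported standard error by k = 1/√(1 − R²). With the stratum balanced by design, the actual size is 2 × (1 − Φ(1.960 × k)).

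**Power, simple version.** Scale the whole signal by 1/k: power = Φ((1.960 + 0.842)/k − 1.960). For R² = 0.05 this is Φ(2.731 − 1.960) = Φ(0.771) = 78.0%.

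**Power, allowing for stratified balance.** Only the reported standard error is inflated, not the true variability of the estimate: power = Φ(1.960 + 0.842 − 1.960 × k). For R² = 0.05 this is Φ(2.802 − 2.011) = Φ(0.791) = 78.5%.

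| Assumed R² | k | Actual size | Power without stratum, simple | Power without stratum, allowing for balance |
|---|---|---|---|---|
| 0.02 | 1.010 | 4.8% | 79.2% | 79.4% |
| 0.05 | 1.026 | 4.4% | 78.0% | 78.5% |
| 0.10 | 1.054 | 3.9% | 75.7% | 76.9% |

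The simple version is the less favourable to the plan, so it serves as the upper end of the loss.

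**Simulation check.** The set-up was 454 patients, 16 centres, allocation balanced within centre and stratum, one post-baseline value per patient, adjustment for baseline and centre, and 2,000 runs. It assumed RMT mean 45, SD 9 and baseline correlation 0.8, none of which is in the documents. At R² = 0.05 and equal device scales, power was 80.2% without the stratum and 81.4% with it. Under no effect at R² = 0.10, the model without the stratum rejected in 4.3% of runs. Monte Carlo error is about 0.9 points for power and 0.5 for size. Both results agree with the formulas in direction and rough size.

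**The case against.** The best defence is that the stratum may carry almost no information here. Finger extension describes the paretic hand. The outcomes are recorded from the unaffected arm, and each is adjusted for its own baseline or pre-stimulation value. Protocol 13.1 links impairment to an imbalance between the two motor cortices. It does not say that finger extension predicts later contralesional RMT or MEP amplitude once the starting value is known. This stands. The loss of power is therefore conditional, and a reader who takes it as established goes beyond the documents. It is also fair that a slightly conservative test does not mislead, and that protocol 8.3 marks contralesional inhibition as optional.

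A reader might also infer that the contralesional models lose power because RMT is a raw stimulator reading, "which is defined as the minimum machine output at which stimulation evokes at least 5 of 10 MEPs", pooled over several stimulators. The documents do not support this:

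- It cannot apply to both models. For the MEP model, "The outcome variable is the contralesional MEP amplitude after cTBS", elicited at 110% of the patient's own RMT, so the stimulus is already scaled to patient and device.
- It does not set the contralesional RMT model apart, because the ipsilesional model uses RMT on the same scale.
- Protocol 6.1 lists five stimulators as available, under a sentence that says three. It does not say which are in use, or that a centre mixes them.
- With one device per centre and assumed scale factors of 0.75 to 1.25, simulated power was 78.5% on the raw scale and 78.9% after rescaling. With factors of 0.9 to 1.1 it was 80.0% for both. Baseline RMT and the centre effect absorb most of the difference. Only with devices mixed within centres did a gap appear (77.8% against 81.2%).
- In a separate simulation with a proportional effect, raw-scale power was 78.7% with equal device scales and 78.6% to 79.2% with unequal ones. The log scale already gave 80.7% with equal scales, so that part of its advantage does not come from the devices.

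Finally, the contralesional RMT model appears to use the session 1 value both as baseline covariate and as an outcome. That is a separate matter, and adding the stratum does not settle it.

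**Conclusion.** The point holds as a minor inconsistency with a free remedy. Both contralesional models omit one of the two randomisation factors, while the plan's other mixed models include both. There is no bias. If the stratum is prognostic after baseline adjustment, the tests are slightly conservative: size is 4.8%, 4.4% or 3.9%, and power is about 79%, 78% or 76% in place of 80%, at assumed R² of 2%, 5% or 10%. The loss is a little smaller once stratified balance is allowed for. These figures rest on the assumed R² and on a reference power of 80%, neither of which the documents give. A very small R² is credible, so the gain should be described as unknown and probably small. Nothing here touches the primary analysis. The documents do not support a claim that mixed stimulators cost these tests power.

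**What to change.** In SAP 7.5, add the finger-extension stratum as a fixed effect to the contralesional RMT model and to the contralesional MEP-amplitude model, in the same form as in the ipsilesional RMT model. Make the same change in protocol 10.3, or state there that the SAP governs. Do this before database lock and unblinding (SAP 5.1), so that the choice cannot depend on the results. The factor is already recorded for every randomised patient. The cost is a few words in the SAP and one model degree of freedom.

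Optionally, add a sentence on how RMT, contralesional and ipsilesional, will be expressed if centres use different stimulators. This would help interpretation only and is not needed for the validity of the tests.
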